## 2 INTRODUCTION

### 2.1 Background and rationale

Decompensated liver cirrhosis (DLC) is characterized by severely impaired liver function and other associated complications, such as portal hypertension, ascites, spontaneous peritonitis, coagulation dysfunction, gastrointestinal bleeding, hepatic encephalopathy, and hepatorenal syndrome [1]. Current available treatment strategies can help improve the patients' quality of life and partially reduce the complications of DLC, and include taking diuretics and following a low-sodium diet, but there are no efficient therapeutic regimens [2, 3]. Furthermore, DLC indicates that the patient is nearing the end stage of liver failure, and liver transplantation then becomes the best option [4]. However, liver transplantation carries considerable risks, since liver failure is frequently associated with liver immune disorders that may contribute to rejection of the new organ and a decrease in the patient's quality of life [2]. In the absence of a liver transplant, an alternative therapy that can effectively relieve the symptoms and promote recovery would be very helpful for patients.

Mesenchymal stem cell (MSC) therapies have emerged as a novel alternative for the treatment of end-stage liver diseases [5, 6]. MSCs have a variety of useful properties, such as the secretion of cytokines, growth factors, and hepatocytes, which can help improve liver functionality and regress fibrosis. Studies have also shown that MSCs can suppress the proliferation of hepatic stellate cells and induce their apoptosis [7-10]. Multiple studies on MSCs have demonstrated their potential for treating end-stage liver disease [11-17], but the appropriate dose and related mechanisms are still unclear. In addition, no clinical research reports have yet explored escalating the dose of MSCs for treating DLC.

## **2.2 Objectives**

We have designed an investigator-initiated, single-arm, dose-escalation clinical trial to evaluate the safety and identify the suitable dose of UC-MSCs as an infusion in patients with decompensated liver cirrhosis. This trial aims to provide evidence for evaluating the safety and efficacy of the UC-MSC infusion in future studies.

## **2.3 Trial design**

This study was an open-label, multiple-dose, dose-escalation, single-armed phase Ib trial (MSC-DLC-1b) to evaluate the safety and efficacy of UC-MSCs for the treatment of patients with DLC. The study comprises three phases: screening + evaluation, 3 + 3 escalation, and follow up. Patients with DLC will be enrolled in the study. Each patient will receive UC-MSCs treatment on days 1, 7, and 14. After treatment, the patients will be followed up for 24 months.

## **3 METHODS**

### **3.1 Study setting**

The trial was conducted in The Fifth Medical Center of PLA General Hospital.

### **3.2 Eligibility criteria**

#### **3.2.1 Inclusion criteria**

1. Willing to provide written informed consent

2. Aged 18 to 75 years (including 18 and 75 years), male or female
3. Patients diagnosed with decompensated liver cirrhosis based on clinical findings, laboratory tests, imaging findings and/or representative pathological findings (decompensated liver cirrhosis is defined as the occurrence of at least one serious complication, including esophageal and gastric varices bleeding, hepatic encephalopathy, ascites, spontaneous bacterial peritonitis and other serious complications)
4. Child-Turcotte-Pugh (CTP) score 7 to 12 points

### **3.2.2 Exclusion criteria**

1. Patients with hepatitis B cirrhosis who had HBV-DNA  $\geq$  the lower limit of test, or who may have discontinued antiviral therapy during the study, or received anti-hepatitis B virus therapy for less than 12 months
2. Patients with hepatitis C cirrhosis who had HCV-RNA  $\geq$  the lower limit of test, or who received anti-hepatitis C virus therapy for less than 12 months
3. Patients under treatment with corticosteroids for autoimmune hepatitis for less than 6 months
4. Trans-jugular intrahepatic portosystemic shunts (TIPS) insertion within 6 months prior to study inclusion
5. Active drinkers with alcohol-related decompensated cirrhosis are unwilling to stop alcohol abuse after inclusion
6. Patients were complicated with biliary obstruction or portal vein cavernous transformation
7. Patients who were known to have other malignant tumors within 5 years before signing informed consent, except for basal cell carcinoma, squamous cell carcinoma and/or carcinoma in situ which had received curative treatment
8. Patients with history of organ transplantation
9. Patients with severe heart, lung, kidney and blood system diseases
10. Patients with drug abuse, drug dependence and patients who receive methadone treatment or with psychosis
11. Patients with history of immunodeficiency disease, including a positive test result for human immunodeficiency virus (HIV) antibodies, or other acquired or congenital immunodeficiency diseases

12. Pregnant or lactating female. Fertile patients who were unable or unwilling to use effective non-pharmaceutical contraception during the trial and within 6 months after the end of the trial
13. Patients with cardiovascular and cerebrovascular events (such as unstable angina pectoris, cerebral hemorrhage, severe ischemic cerebral infarction) within 3 months before the first dose; Myocardial infarction or clinically significant cardiac rhythm or conduction abnormalities within 12 months before the first dose
14. Patients with allergic constitution (history of allergy to more than two foods or drugs) or history of severe allergy, or known severe allergy to the investigational drug or any of the excipients
15. Patients who have received previous stem cell therapy or are intolerant to cell therapy
16. Participants in other clinical trials within the past 3 months
17. Patients with any other condition considered by the investigator to be ineligible for participation in the study

### **3.3 Interventions**

#### **3.3.1 Investigational medicinal product**

The UC-MSCs (VUM02,  $5 \times 10^7$  cells/10 mL/bag) will be prepared by Wuhan Optics Valley Vcanbiopharma Co., Ltd., in China. Briefly, mesenchymal stem cells (MSCs) will be obtained according to the method described in our previous study [18]. Umbilical cord tissue for sampling will be selected and collected after the mothers have signed the informed consent form. After the blood vessels are removed from the umbilical cord tissue, it will be cut into small pieces of about 1–2 mm^3, uniformly inoculated in cell culture flasks for isolation of the MSCs, and the primary cells will be digested with TrypLE digestive enzyme for 10–13 days. The primary cells will be inoculated in cell culture flasks at a density of about  $2 \times 10^4$ /cm^2 and cultured in an incubator at 37 °C with a volume fraction of 5% CO2 and saturated humidity. After being passaged for P4 generation, the cells will be cryopreserved for use as the working cell bank. Subsequently, safety and biological performance tests will be conducted on the working cell bank. Following successful testing, the cells will undergo a resuscitation culture for 48 to 72 h to prepare P5 generation cell formulations. The cells must meet strict criteria to be used in our study. Specifically, the expression of cell immunophenotypes CD90, CD105, CD73 must be greater than 95%; the

expression of CD45, CD34, CD14, CD19, and HLA-DR must be lower than 2%; the cells must test negative for sterility and mycoplasma; and the intracellular toxins must be less than 1 EU /mL. Only UC-MSCs that pass these tests will be used for the clinical trials.

### **3.3.2 Standard of care(SOC)**

Provide optimal support and medication in accordance with relevant latest clinical guidelines.

### **3.3.3 Intervention assignment**

This study is an open-label, multiple-dose, dose-escalation, single-armed phase Ib trial. In this study, a total of two dose groups ( $1.0 \times 10^8$  cells,  $2.0 \times 10^8$  cells) are set up, multiple dose escalation will be performed according to the "3+3" rule, each subject will be only entered into one corresponding dose group. See Section 3.8 for details.

### **3.3.4 Modifications of intervention**

Subjects in each corresponding dose group who experience grade 3 or higher adverse events within one week after the first HUC-MSCs treatment may have their second HUC-MSCs treatment delayed by one week or terminated based on the specific clinical situation, and the assessment content and process must be recorded in detail.

## **3.4 Outcomes**

### **3.4.1 Primary outcomes**

The primary outcomes are the incidence of DLTs, adverse events(AEs), MTD and the change in the MELD score from baseline to the 28th day after the first dose intervention.

### **3.4.2 Secondary outcomes**

The secondary outcomes include:

1. Change in the MELD score from baseline to 7 days, 14 days, 21 days, 2 months, 3 months, 6 months, 12 months, 18 months and 24 months after the intervention
2. Incidence of each complication associated with decompensated cirrhosis
3. Liver transplant-free survival
4. Incidence of liver failure

5. Plasma albumin (ALB) level
6. Plasma prealbumin (PALB) level
7. Total bilirubin (TBIL)
8. Serum cholinesterase (CHE)
9. Prothrombin time (PT)
10. Child-Turcotte-Pugh (CTP) score
11. EuroQol Group 5-Dimension Self-Report Questionnaire (EQ-5D) scale score
12. Incidence of liver cancer
13. Chronic Liver Disease Questionnaire (CLDQ) score

### **3.5 Participant timeline**

## Assessment schedule for the patients with decompensated cirrhosis

|                                                 | Screening    | Period of treatment |                   |                    | Observation period after treatment |                     |                         |                         |                         | Long-term safety follow-up |                          |                          |
|-------------------------------------------------|--------------|---------------------|-------------------|--------------------|------------------------------------|---------------------|-------------------------|-------------------------|-------------------------|----------------------------|--------------------------|--------------------------|
| Timepoint                                       | Day -21 to 0 | Day 1 $\pm$ 0 day   | Day 7 $\pm$ 0 day | Day 14 $\pm$ 0 day | Day 21 $\pm$ 1 day                 | Day 28 $\pm$ 1 days | Month 2
$\pm$ 7 days | Month 3
$\pm$ 7 days | Month 6
$\pm$ 7 days | Month 12
$\pm$ 7 days   | Month 18
$\pm$ 7 days | Month 24
$\pm$ 7 days |
| Enrollment and informed consent                 | ×            |                     |                   |                    |                                    |                     |                         |                         |                         |                            |                          |                          |
| Screening table                                 | ×            |                     |                   |                    |                                    |                     |                         |                         |                         |                            |                          |                          |
| Demographic data                                | ×            |                     |                   |                    |                                    |                     |                         |                         |                         |                            |                          |                          |
| Allergies and family history                    | ×            |                     |                   |                    |                                    |                     |                         |                         |                         |                            |                          |                          |
| Past medical history and treatment history      | ×            |                     |                   |                    |                                    |                     |                         |                         |                         |                            |                          |                          |
| Existing disease and concomitant treatment      | ×            |                     |                   |                    |                                    |                     |                         |                         |                         |                            |                          |                          |
| Vital signs                                     | ×            | ×                   | ×                 | ×                  | ×                                  | ×                   | ×                       | ×                       | ×                       | ×                          | ×                        | ×                        |
| Physical examination                            | ×            | ×                   | ×                 | ×                  | ×                                  | ×                   | ×                       | ×                       | ×                       | ×                          | ×                        | ×                        |
| Hepatitis B blood test/ HCV antibody            | ×            |                     |                   |                    |                                    |                     |                         |                         | ×                       | ×                          | ×                        | ×                        |
| HIV/TP antibody                                 | ×            |                     |                   |                    |                                    |                     |                         |                         |                         |                            |                          |                          |
| Blood routine test                              | ×            | ×                   | ×                 | ×                  | ×                                  | ×                   | ×                       | ×                       | ×                       | ×                          | ×                        | ×                        |
| Urine routine test                              | ×            | ×                   | ×                 | ×                  |                                    | ×                   | ×                       | ×                       | ×                       | ×                          | ×                        | ×                        |
| Urine pregnancy test                            | ×            |                     |                   |                    |                                    |                     |                         |                         |                         |                            |                          |                          |
| Stool routine test + occult blood               | ×            | ×                   | ×                 | ×                  |                                    | ×                   | ×                       | ×                       | ×                       | ×                          | ×                        | ×                        |
| Blood biochemistry test                         | ×            | ×                   | ×                 | ×                  | ×                                  | ×                   | ×                       | ×                       | ×                       | ×                          | ×                        | ×                        |
| Coagulation function test                       | ×            | ×                   | ×                 | ×                  | ×                                  | ×                   | ×                       | ×                       | ×                       | ×                          | ×                        | ×                        |
| Blood ammonia                                   | ×            | ×                   | ×                 | ×                  | ×                                  | ×                   | ×                       | ×                       | ×                       | ×                          | ×                        | ×                        |
| AFP                                             | ×            | ×                   | ×                 | ×                  | ×                                  | ×                   | ×                       | ×                       | ×                       | ×                          | ×                        | ×                        |
| Electrocardiogram                               | ×            | ×                   | ×                 | ×                  | ×                                  | ×                   | ×                       | ×                       | ×                       | ×                          | ×                        | ×                        |
| Chest X-ray or CT                               | ×            |                     |                   |                    |                                    |                     |                         |                         |                         | ×                          |                          | ×                        |
| Abdominal ultrasound examination                | ×            | ×                   |                   |                    | ×                                  | ×                   | ×                       | ×                       | ×                       | ×                          | ×                        | ×                        |
| Elastography                                    | ×            |                     |                   |                    |                                    | ×                   |                         | ×                       |                         |                            |                          |                          |
| Gastroscopy                                     | ×            |                     |                   |                    |                                    |                     |                         |                         | ×                       |                            |                          |                          |
| Upper abdominal CT/MRI plain scan + enhancement | ×            |                     |                   |                    |                                    |                     |                         |                         | ×                       | ×                          | ×                        | ×                        |
| MELD score                                      | ×            | ×                   | ×                 | ×                  | ×                                  | ×                   | ×                       | ×                       | ×                       |                            |                          |                          |

## Protocol

|                                                                 |   |   |   |   |   |   |   |   |   |   |   |   |
|-----------------------------------------------------------------|---|---|---|---|---|---|---|---|---|---|---|---|
| Child-Pugh score                                                | × |   |   |   | × | × | × | × | × |   |   |   |
| QoL scale                                                       | × | × |   |   | × | × | × | × | × | × | × | × |
| Collection of samples for omics research (blood sample + stool) |   | × | × | × | × | × | × | × | × |   |   |   |
| Infusion records                                                |   | × | × | × |   |   |   |   |   |   |   |   |
| Adverse events                                                  |   | × | × | × | × | × | × | × | × | × | × | × |
| Concomitant medication/treatment                                | × | × | × | × | × | × | × | × | × | × | × | × |

### **3.6 Sample size**

This is a proof-of-concept study. A total of 3-6 patients will be recruited for each dose cohort, comprising low and high dose groups, with 3 patients in each cohort initially. The additional patients will be added to the cohort if dose-limiting toxicity is presented. A total of 6-12 patients will be recruited for the study [19].

### **3.7 Recruitment**

Patient will be recruited from The Fifth Medical Center of PLA General Hospital. No other recruitment strategy (e.g., advertisement) will be adopted in this study.

### **3.8 Allocation and product management**

#### **3.8.1 Allocation**

This study is an open-label, multiple-dose, dose-escalation, single-armed phase Ib trial. In this study, a total of two dose groups ( $1.0 \times 10^8$  cells,  $2.0 \times 10^8$  cells) are set up, multiple dose escalation will be performed according to the "3+3" rule, each subject will be only entered into one corresponding dose group.

#### **3.8.2 Dose escalation and dose-limiting toxicity**

In this study, a total of two dose groups ( $1.0 \times 10^8$  cells,  $2.0 \times 10^8$  cells) were set up, multiple dose escalation was performed according to the "3+3" rule, each subject was only entered into one corresponding dose group. Starting from the low-dose group ( $1.0 \times 10^8$  cells), each subject was closely observed for 7 days after the corresponding dose of UC-MSCs treatment, and the possible DLTs were evaluated. Subjects in the same dose group must complete the DLT assessment for 7 days before starting the next subject, and the first patient in the high-dose group ( $2.0 \times 10^8$  cells) could not be enrolled until the last patient in the low-dose group ( $1.0 \times 10^8$  cells) had completed a 28-day safety assessment. During dose escalation, safety data from the previous dose group were used by the investigator and the sponsor to determine whether to proceed with the next dose.

During the observation period of DLT, if none of the 3 subjects in a dose group observed DLT (0/3), they could be escalated to the next dose group. If there was one DLT (1/3) in a dose group, 3

additional subjects in this dose group were required, and if the 3 additional subjects had no DLT (total DLT 1/6), they could escalate to the next dose group. If one or more DLTs (total DLTs  $\geq 2/6$ ) occurred in the supplementary 3 patients, the dose escalation was terminated, and the previous dosage was MTD. If no DLT occurred after the completion of dose escalation in either dose group, the decision to continue dose escalation was made in joint discussion between the investigator and the sponsor. The specific rules for dose escalation can be found in **Figure 1** [19].

[figure not shown]

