**Figure 1 Dose escalation flowchart**

### 3.8.3 Assessment of DLT and MTD

DLT will be evaluated according to the National Cancer Institute Common Toxicity Criteria (NCI-CTC) 5.0 ([https://ctep.cancer.gov/protocoldevelopment/electronic\\_applications/ctc.htm](https://ctep.cancer.gov/protocoldevelopment/electronic_applications/ctc.htm)). DLT is defined as any grade 4 hematological toxicity; grade 3 thrombocytopenia with hemorrhage; grade 3 or greater nausea, vomiting or, diarrhea or any grade 3 or greater treatment-related non-hematological toxicity (excluding alopecia and fatigue). Groups of three patients will be recruited at a time and allocated to their respective cohorts, starting with the lowest dose. For each cohort, one patient will be given the treatment at first and then observed for 3 days for signs of DLT. The next patient's treatment will only begin after the first patient has undergone 3 days of observation. The treatment of another cohort start after the previous cohort has experienced at least 7 days of observation.

The trial will proceed as follows to ensure safe dose escalation and determine the MTD: (1) If there is no DLT observed in all three patients of a cohort, the trial will proceed to the next dose cohort; (2)

If one of the three patients of a cohort experiences DLT, then three more patients will be included and tested in this dose cohort. If still only one of the six patients experiences DLT, the trial will proceed to the next dose cohort. However, if two or more of the six patients experience DLT, the previous dose will be considered as the MTD; (3) If two or all three of the three initial patients experience DLT in a cohort, the MTD will remain undetermined.

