**Figure 1 Dose escalation flowchart**

### 3.8.3 Assessment of DLT and MTD

DLT will be evaluated according to the National Cancer Institute Common Toxicity Criteria (NCI-CTC) 5.0 ([https://ctep.cancer.gov/protocoldevelopment/electronic\\_applications/ctc.htm](https://ctep.cancer.gov/protocoldevelopment/electronic_applications/ctc.htm)). The following drug-related adverse events were considered DLTs: (1) Grade  $\geq 3$  allergic reactions related to UC-MSCs, such as dyspnea, chills and fever; (2) Grade  $\geq 3$  embolic adverse events related to UC-MSCs, such as acute pulmonary embolism, deep vein thrombosis, etc.; (3) Grade  $\geq 3$  hematological toxicity related to UC-MSCs; (4) Any unexpected toxicity requiring discontinuation of treatment at the discretion of the investigator and sponsor.

During the observation period of DLT, if none of the 3 subjects in a dose group observed DLT (0/3), they could be escalated to the next dose group. If there was one DLT (1/3) in a dose group, 3 additional subjects in this dose group were required, and if the 3 additional subjects had no DLT (total DLT 1/6), they could escalate to the next dose group. If one or more DLTs (total DLTs  $\geq 2/6$ )

occurred in the supplementary 3 patients, the dose escalation was terminated, and the previous dosage was MTD. If no DLT occurred after the completion of dose escalation in either dose group, the decision to continue dose escalation was made in joint discussion between the investigator and the sponsor.

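### In 1b the DLT observation period has no stated start or end, and its only stated length, 7 days, does not fit infusions on days 1, 7 and 14, so DLT incidence and MTD may describe mainly the first infusion

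*Supplement*

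**What the plan says.** All references are to the MSC-DLC-1b protocol in the Supplement unless 1a is named.

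- **Regimen.** Section 2.3: "Each patient will receive UC-MSCs treatment on days 1, 7, and 14". The schedule in section 3.5 gives these three days a tolerance of zero.
- **Observation and stagger.** Section 3.8.2: "each subject was closely observed for 7 days after the corresponding dose of UC-MSCs treatment". It adds: "Subjects in the same dose group must complete the DLT assessment for 7 days before starting the next subject".
- **Between dose groups.** Section 3.8.2 keeps the high-dose group closed until the last low-dose patient "had completed a 28-day safety assessment". The investigator and sponsor use the earlier group's safety data to decide whether to proceed.
- **Counting rule.** Sections 3.8.2 and 3.8.3 run the 3+3 tally over a named period: "During the observation period of DLT, if none of the 3 subjects in a dose group observed DLT (0/3". No start or end day is given. Figure 1, cited for the specific rules, is not shown.
- **DLT definition.** Section 3.8.3 has four items, none with a time limit. The first three are related grade 3 or higher allergic, embolic and haematological events. The fourth is "Any unexpected toxicity requiring discontinuation of treatment at the discretion of the investigator and sponsor".
- **Modification rule.** Under section 3.3.4, patients with a grade 3 or higher event in the week after infusion 1 "may have their second HUC-MSCs treatment delayed by one week or terminated based on the specific clinical situation". It says nothing about events after infusions 2 or 3.
- **Primary outcomes.** Section 3.4.1 lists DLT incidence, adverse events, MTD and the MELD change to day 28 after the first dose.

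**The concern.** What sets 1b apart from 1a is repeated dosing, so its primary tolerability result should describe the three-infusion course. The one DLT assessment with a stated length lasts 7 days, and the text does not say which infusion starts the clock. The two natural readings give different tallies. One leaves out nearly everything after infusion 2. The other contradicts the rule for starting the next patient.

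The definition adds to this. A related toxicity that is not allergic, embolic or haematological qualifies only through item 4, which depends on stopping treatment. Once infusion 3 has been given in full, no planned treatment remains to stop, so item 4 has little or no effect exactly when cumulative exposure is highest.

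At stake is what a tally such as 0/3 means. It could be reported as tolerability of the repeated-dose regimen when it rests mainly on the first infusion.

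**Working it through.** **1. The plan's own figure.** Section 3.6 and the trial summary give 6 to 12 patients. Two cohorts of 3 to 6 give 2 × 3 = 6 and 2 × 6 = 12, which agrees. The sample size is not in question.

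**2. The 7-day window against the infusion days (1, 7, 14).**

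| Reading | Window ends | Days seen after infusion 2 | Days seen after infusion 3 |
|---|---|---|---|
| From infusion 1, Day 1 counted as the first day | Day 7 | 0 | 0 |
| From infusion 1, Day 1 + 7 | Day 8 | 1 | 0 |
| 7 days from each infusion | Day 14 + 7 = 21 | 7 | 7 |
| For comparison, the Day 28 assessment | Day 28 | 28 − 7 = 21 | 28 − 14 = 14 |

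**3. The stagger.** If the next patient may start after 7 days, the three patients can start on calendar days 1, 8 and 15. Patient 1 has 7 days of follow-up after infusion 3 only on calendar day 21. All three patients can thus have begun dosing before anyone has 7 days of follow-up after the full course. If instead the assessment covers each infusion, the next patient could not start until about day 21, which is not a single 7-day assessment.

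**4. Illustration of size.** The documents give no DLT risk. Assume a constant, independent risk q per infusion.

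- Patient-level risk seen if only infusion 1 counts: q.
- Patient-level risk seen if all three count: p = 1 − (1 − q)³.
- Chance that a cohort passes the 3+3 rule at risk r (0/3, or 1/3 followed by 0/3): (1 − r)³ + 3r(1 − r)⁵.
- Share of patients with a DLT in the course who have none at infusion 1: (p − q)/p.

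| q | p | Pass, infusion 1 only | Pass, all three | Share outside |
|---|---|---|---|---|
| 2% | 5.9% | 0.9954 | 0.9640 | 66% |
| 5% | 14.3% | 0.9734 | 0.8285 | 65% |
| 10% | 27.1% | 0.9061 | 0.5548 | 63% |

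Worked line for q = 5%: p = 1 − 0.95³ = 0.1426. Infusion 1 only: 0.95³ + 3 × 0.05 × 0.95⁵ = 0.8574 + 0.1161 = 0.9734 (from unrounded terms). All three: (1 − p)³ + 3p(1 − p)⁵ = 0.6302 + 0.1982 = 0.8285 (0.82848 unrounded, so 82.8%).

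These figures take the narrowest window and ignore the 28-day review before the high-dose group opens.

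**The case against.** The best defence is that the sentence about starting the next patient is a stagger rule rather than a counting window. The sentence before it, about observation after the corresponding dose, can mean after each infusion. Items 1 to 3 of the definition carry no time limit and can apply after any infusion. Late toxicity is also not lost. Adverse events are themselves a primary outcome and are recorded through month 24. The 28-day safety assessment and the safety-data decision come before any high-dose patient. Figure 1 might define the period, and section 3.10.1 promises a more detailed analysis plan that is not shown.

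Much of this stands. A reader might infer more than the text supports in five ways:

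- **That DLTs after infusions 2 and 3 are excluded, or were missed.** The text allows their exclusion but does not require it, and nothing shows that any were missed.
- **That item 4 cannot operate at infusion 3.** A toxicity that stops that infusion while it runs could still qualify. Only events after it is complete are affected.
- **That the 1b definition is simply narrower than the one in 1a.** 1a does count "any grade 3 or greater treatment-related non-hematological toxicity (excluding alopecia and fatigue"), which 1b does not list as such. But 1b counts related grade 3 haematological toxicity, whereas 1a asks for grade 4, or grade 3 thrombocytopenia with haemorrhage. The definitions differ in both directions.
- **That a patient stopped under section 3.3.4 counts as DLT-free.** No section says so, and item 4 would make some of these stops DLTs. For the rest the text is silent.
- **That the first window is still open when infusion 2 is given.** That depends on whether Day 1 is counted as the first day.

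What the defence does not remove is the conflict. Reading the window as per infusion rescues coverage but breaks the stagger rule. The 28-day assessment is not called the DLT period. It is stated only as the condition for opening the high-dose group, not between patients within a cohort or before an MTD is declared after the high-dose group. Recording an event as an adverse event does not put it into the DLT tally.

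**Conclusion.** The concern holds as an unreconciled definition of two primary outcomes. The DLT period has no start or end in the visible text, and the only stated length either misses almost all follow-up after infusion 2 and all of it after infusion 3, or conflicts with the rule for starting the next patient. DLT incidence and MTD in 1b may therefore describe mainly the first infusion.

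The size is uncertain. On the assumed risks, the difference in the chance of passing the 3+3 rule is about 3 percentage points at 2% per infusion (99.5% − 96.4%), about 14 at 5% (97.3% − 82.8%) and about 35 at 10% (90.6% − 55.5%). These values rest on an invented, constant and independent risk and on the narrowest window. They show the direction and are not an estimate for this product.

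The consequence is for labelling and interpretation more than for detection, since late events remain visible as adverse events and at the 28-day assessment. The trial summary reports that all dose groups have completed 28 days after the first dose. New wording would therefore not change the dosing already given, but it would change what the reported tally can be said to show.

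**What to change.** **Protocol.** The sponsor and investigator should reconcile sections 2.3, 3.3.4, 3.5, 3.8.2 and 3.8.3 of 1b, with Figure 1, so that one DLT period with a stated start and end applies to both the 3+3 tally and the primary outcome. Which period is right is for them to decide.

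**Analysis.** In the detailed analysis plan still to come, specify one table for each dose group showing:

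- events that meet the DLT criteria, by the infusion they followed and cumulatively through the existing Day 28 assessment;
- all related grade 3 or higher events, laid out in the same way, so that late events outside items 1 to 3 can be seen;
- the number of infusions each patient received.

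**Reporting.** Limit the tolerability conclusion to the infusions that the DLT tally covered. If it covered only the first, say so beside the DLT incidence and MTD.

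**Cost.** The change needs protocol wording and one extra table, drawn from adverse-event and infusion records that the schedule already collects, with no added visit. The reported toxicity may look less favourable.
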